## Abstract

**Background:**

Thin endometrium negatively impacts the reproductive function. Current treatments for thin endometrium do not always improve endometrial receptivity. Preliminary evidence suggests that electroacupuncture could have potential therapy for thin endometrium in infertile women. Thus, this randomized controlled trial was designed to test whether electroacupuncture can improve endometrial receptivity in infertile women with thin endometrium.

**Methods:**

This study is a randomized, single-blinded, controlled, clinical trial. A total of 142 eligible patients will be recruited and randomly assigned to the electroacupuncture (EA) group or the sham electroacupuncture (SEA) group in a 1:1 ratio. Participants will receive 36 sessions over three menstrual cycles (12 weeks in total), with the same acupoint prescription. The primary outcome of this trial is endometrial thickness in the midluteal phase. The secondary outcomes include endometrial pattern, resistance index (RI) and pulsatility index (PI) of bilateral uterine artery and endometrium blood flow, serum estradiol (E2) and progesterone (P), and pregnancy rate. The pregnancy rate will be evaluated during a 6-month follow-up after completion of the trial. All other outcomes will be evaluated before treatment, during the treatment of 1st, 2nd, and 3rd menstrual cycle, and 6 months after treatment.

**Discussion:**

If the outcome confirms the effectiveness of electroacupuncture for thin endometrium in infertile women, this treatment will be proposed for application in clinical practice.

**Trial registration:**

Chinese Clinical Trials Registry ChiCTR2000029983. Registered on 18 February 2020

**Supplementary Information:**

The online version contains supplementary material available at 10.1186/s13063-021-05029-7.

## Background

Previous research has shown that endometrial thickness is related to endometrial receptivity [1]. An inadequate endometrium can be considered as a main hindrance to fertility [2]. It has been shown that thin endometrium leads to infertility [3]. Likewise, a “thin” endometrium is associated with implantation failure and low implantation rates [1, 4]. Globally, 8 to 12% of reproductive age couples suffer from infertility which has become a major global public health issue [5]. Despite the advances in assisted reproduction, many patients with thin endometrium repeated implantation failure [6]. It has been reported that nearly two-thirds of failed implantation in IVF (in vitro fertilization) are caused by poor endometrial receptivity [7]. Incidences of thin endometrium in ovarian stimulation cycles and natural cycles are 38–66% [8] and 5–25% [9], respectively. In fresh or frozen-thawed embryo transfer cycles, thin endometrium often leads to cancelation of ET and cryopreservation of all the embryos [10]. A thin endometrium is associated with low conception rate [11–13], but also to a higher probability of spontaneous abortion and ectopic pregnancy [14]. The probability of clinical pregnancy was 23.3% for an endometrium measuring ≤ 7 mm, which was significantly lower than that of endometrium measuring > 7 mm (48.1%) [13]. The lowest pregnancy rates were associated with endometrial thickness of < 7 mm in 768 consecutive medicated FER (frozen embryo replacement) cycles [15]. Hence, thin endometrium is often defined as less than 7 mm during the late follicular phase or after ovulation [16, 17]. Endometrial receptivity appears to be the bottleneck of the reproductive process [18]. Therefore, improving endometrial receptivity among infertile patients with thin endometrium is urgently needed in reproductive medicine.

The endometrium, a unique cyclic tissue regeneration system, depends on the cyclical growth and regression of blood vessels that supply the endometrium [19]. Previous works showed that angiogenesis which depends on the expression of angiogenic factors (VEGF, FGF, and angiopoietin families) is a critical factor in determining the endometrial receptivity during the implantation window (IW) [20]. Thin endometria are characterized by high uterine blood flow impedance, poor growth of glandular epithelium, decreased expression of vascular endothelial growth factor (VEGF), and poor vascular development [21]. Current therapeutic strategies for thin endometrium include long-term administration of exogenous estrogen, low-dose of aspirin, vaginal sildenafil citrate application, transvaginal endometrial perfusion of granulocyte colony-stimulating factor (G-CSF), autologous platelet-rich plasma infusion (PRP), stem cell therapy, vitamins C and E, and L-arginine supplement [8, 22]. Despite the vast diversity of treatment, most of these treatment options result in a minor change in the endometrium thickness and pregnancy rate [22]. Currently, there is no one acceptable approach to treat thin endometrium [23], thus the need for an alternative and complementary therapy for patients with thin endometrium.

Acupuncture may have a potential therapeutic effect on thin endometrium in infertile women. Pulsatility index (PI) in the uterine arteries is considered valuable in assessing endometrial receptivity, and it was found to have decreased after EA treatment [24]. EA has been found to improve endometrial angiogenesis during peri-implantation period by increasing the expression of VEGFR2/PI3K/AKT and VEGFR2/ERK signaling pathways in COH rats [25]. Estrogen promotes the reconstruction of the endometrial vascular system and the repair of damaged endometrium by binding to the estrogen receptor (ER) ligand [26]. A significant increase in endometrial thickness and the number of endometrial glands after EA treatment, probably due to up-regulation of serum E levels, and different regulation of the sex steroid receptors ERα and ERβ [27]. EA also plays an effective auxiliary role of supporting bone marrow mesenchymal stem cell (BMSCs) in repair of thin endometrium [28]. Furthermore, acupuncture may ameliorate the uterine environment by increasing the glandular area and expression of receptivity markers such as LIF and OPN proteins [29]. Clinical studies have found that acupuncture may improve the high-quality embryo rate [30] and clinical pregnancy rate [31] by improving endometrial blood flow state and the uterine environment. Although acupuncture has initially been shown to improve endometrial receptivity and pregnancy rates during the process of assisted reproduction, the associated evidence base is poor [32]. Thus, well-designed RCT should be conducted based on a rigorous methodology to evaluate the efficacy of EA in improving endometrial receptivity for thin endometrium in infertile women.

## Methods/design

### Study design

A single-center, patient-blinded, randomized controlled trial (RCT) was devised following the Consolidated Standards of Reporting Trials (CONSORT) statement [33], the Standardized Protocol Items: Recommendations for Interventional Trials (SPIRIT) guidelines [34], and the Revised Standards for Reporting Interventions in Clinical Trials of Acupuncture (STRICTA) [35]. If participants are eligible and agree to participate, they will be randomly assigned to electroacupuncture group (EA) or sham-electroacupuncture (SEA) group in a 1:1 ratio. The trial will be conducted in the Department of gynecology, Chengdu University of Traditional Chinese Medicine Affiliated Hospital. The flowchart is shown in Fig. 1.

**Fig. 1 Fig1:**
[figure not shown]
Trial flow chart

### Ethics

The trial will be carried out in accordance with the Declaration of Helsinki [36]. Ethical approval has been obtained from the Sichuan Regional Ethics Review Committee on Traditional Chinese Medicine with an ethics approval number of 2019KL-072. The work reported in this article is registered with an identifier (ChiCTR2000029983) by the Chinese Clinical Trial Registry.

### Participants

The diagnostic criteria for thin endometrium are based on data provided in our previous studies: endometrial thickness (EMT) < 7 mm in the mid-luteal phase (7 days after the day of ovulation or on day 21 of an unstimulated ovarian cycle) [8, 15, 17]. Infertility will be diagnosed as the failure to conceive for at least 12 months of unprotected sexual intercourse [37].

### Inclusion criteria

Patients who conform to the following criteria will be included:
Females, aged between 20 and 45 years;Meets the diagnosis of infertility and is trying to conceive;EMT < 7 mm in the midluteal phase;Willing to participate in this study and sign an informed consent form.

### Exclusion criteria

Infertility induced by an ovulation disorder, severe endometriosis, Asherman’s syndrome, luteal phase deficiency, fallopian tube obstruction, or male infertility;Pregnancy or lactation;History of psychiatric disorders (serious anxiety and depression, schizophrenia), coagulation disorders, blood infections (viral hepatitis, HIV), malignant tumor, diabetic neuropathy or complicated with serious heart, kidney or liver disease;A cardiac pacemaker, metal allergy, or artificial joint;History of acupuncture treatment in the last 3 months or use of estrogen, progestin in the past 4 weeks;Participation in other clinical trials within the past 3 months.

### Dropout criteria

Patients who quit the study voluntarily or have poor clinical compliance during observation period or found to not conform to the inclusion criteria after enrolment will be considered as having dropped out.

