### Randomization

The participants will be randomly assigned to electroacupuncture group or sham-electroacupuncture group in a 1:1 ratio. Randomization will be performed based on a random list of numbers generated by SPSS21.0 software (International Business Machines Corp., Armonk, NY). Allocation will be conducted by a designated researcher who has no contact with any participant and is not involved in the data collection or analysis. Allocation will be concealed in sequentially numbered, opaque, and sealed envelopes containing the randomization assignments. The appropriate numbered, opaque, sealed envelope will be opened after each participant meets eligibility criteria and signs informed consent. The allocation concealment to the doctors is not feasible for trials on acupuncture. The acupuncturist will not be allowed to reveal any information about treatment procedures and outcomes to the participants or the assessor.

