### Blinding

The specific nature of the intervention makes it impossible to blind the acupuncturist. However, the participants, data collection staff, and data analysts will be blinded. To maximize blinding of participants, placebo needles and sham electroacupuncture design will be used in the sham-electroacupuncture group. Adhesive pads will be applied to both EA and SEA groups to ensure that the participants are unaware of the differences between the two acupuncture treatments. Each participant will receive intervention in a personal space separated by bed curtain and no communication will be allowed between participants. During the intervention period, the acupuncturist and the data collection researcher will not be allowed to exchange information on grouping, treatment procedures, and outcomes. Blinded evaluation and blinded statistical analysis will be emphasized during the data collection and analysis stage.

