### Outcome measures

#### Primary outcome

The primary outcome will be endometrial thickness in the mid-luteal phase of the 3rd menstrual cycle (the primary time frame), the 1st menstrual cycle and 2nd menstrual cycle as well as 6 months after completion of the treatment (the secondary time frame) compared with baseline (in the − 1st menstrual cycle).

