#### Sample size

There is insufficient previous data on endometrial thickness after treatment with EA in infertile women with thin endometrium. Besides, the effect of acupuncture varies with different acupoint selection. The aim of the research was to clarify the effects of EA on thin endometrium in infertile women. Therefore, the change in endometrial thickness will be used as an evaluation index. Based on our pilot study, changes in endometrial thickness of the mid-luteal phase after a 12-week treatment were shown to be 8.30 ± 2.83 mm (*n* = 10) in the electroacupuncture group (EA) and 7.10 ± 1.97 mm (*n* = 9) in the sham electroacupuncture group (SEA). Measurement data of parallel control trials (1:1) will be analyzed statistically using the following formula for sample size estimation:
$$ n=\frac{{\left({Z}_{\alpha }+{Z}_{\beta}\right)}^2\ast 2{\sigma}^2}{\delta^2} $$

With a 5% significance level (*α* = 0.05, two-sided) and 80% power (*β* = 0.2), at least 62 patients should be enrolled in each group and a total of 142 participants will be recruited to allow for a 15% dropout rate.

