#### Statistical analysis

Statistical analyses of data will be performed using SPSS21.0 software (International Business Machines Corp., Armonk, NY) by analysts who will be blinded to the patients’ allocation. To evaluate the curative effect in this trial, an intention-to-treat analysis (ITT) will be performed. Categorical variables will be presented by frequency (percentage) and analyzed with the chi-squared test or Fisher’s exact test. Continuous variables will be presented as mean ± standard deviation (M ± SD) if they meet normal distribution. Otherwise, they will be presented as medians ± interquartile range (M ± IQR). The demographic characteristics will be compared between the groups by independent *t* tests at baseline. All longitudinal analyses for continuous variables measured at baseline and three-time periods will be performed using linear mixed modeling. Comparisons between the intervention and control groups will be performed using the chi-square test or Fisher s exact test, as appropriate, for categorical variables. To evaluate the safety of acupuncture, we will use a Fisher exact test to report the relative risk of an adverse effect. All the tests will be two-sided, and a *P* value of less than 0.05 will be considered to be statistically significant.

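### The dropout rule covers randomised women who comply poorly or are later found ineligible, and the protocol does not reconcile this with its intention-to-treat analysis

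*Protocol article*

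**What the plan says.** Four places in the protocol article bear on this.

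- **Dropout criteria.** Women who leave of their own accord are dropouts, and so are two groups who need not have left: "poor clinical compliance during observation period or found to not conform to the inclusion criteria after enrolment will be considered as having dropped out".
- **Randomization.** The "sealed envelope will be opened after each participant meets eligibility criteria and signs informed consent". Anyone reclassified during treatment therefore already has an allocation.
- **Sample size.** The calculation concludes that "at least 62 patients should be enrolled in each group", and recruitment is raised to 142 in total for 15% dropout.
- **Statistical analysis.** It states that "an intention-to-treat analysis (ITT) will be performed" and adds: "All longitudinal analyses for continuous variables measured at baseline and three-time periods will be performed using linear mixed modeling". It does not say how women classed as dropouts enter that analysis.

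The Blinding section says of the treating practitioner: "The specific nature of the intervention makes it impossible to blind the acupuncturist". Participants, data collection staff and analysts are to be blinded.

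**The concern.** Intention-to-treat keeps every randomised woman in her allocated arm whatever happens to her treatment. A rule that turns poor attendance or a late eligibility finding into dropout pulls the other way, because in ordinary use a dropout is someone whose later measurements are not taken.

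Poor compliance is the more serious half. It occurs after allocation, and the two arms ask different things of the participant. The active arm has needle insertion, Deqi and current; the sham has none of these. Tolerance of 36 sessions could therefore differ by arm, and women who tolerate treatment badly may also differ in endometrial thickness. Losing their third-cycle scans would then leave arms that are no longer comparable.

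Late-found ineligibility is weaker. Age, infertility history and baseline thickness are settled before allocation, and treatment cannot cause a failure on them.

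The matter cannot simply wait for an analysis plan, because it affects data collection. A scan that is not taken in the third cycle cannot be recovered by any later choice of analysis set.

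**Working it through.** **1. How the sample size treats dropouts**

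Inputs from the Sample size section: pilot values 8.30 (SD 2.83) and 7.10 (SD 1.97), two-sided alpha 0.05, power 0.80.

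- Target difference: 8.30 − 7.10 = 1.2 mm.
- Simple average of the SDs: (2.83 + 1.97)/2 = 2.40 mm.
- n = 2 × 2.40² × (1.960 + 0.842)² / 1.2² = 62.79, against the stated 62.
- Inflation: 124 × 1.15 = 142.6, against the stated 142, or 71 per arm.

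The stated figures reproduce to within rounding. The inflation has a purpose only if a dropout does not contribute to the primary comparison. Under the Dropout criteria, that same word includes poor compliers and women found ineligible later. This supports reading them as lost to the analysis, but it does not prove it.

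**2. Bias if such women are removed**

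Let f be the share removed from an arm, and g the amount by which the removed women's mean thickness lies below that of the women retained. The full-arm mean is the retained mean minus f × g, so removal raises the arm mean by f × g. With the same g in both arms:

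bias in the difference = (f in EA − f in sham) × g

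The protocol gives neither f by arm nor g, so every value below is assumed.

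| Removed, EA / sham | g = 0.5 mm | g = 1 mm | g = 2 mm |
|---|---|---|---|
| 15% / 15% | 0 | 0 | 0 |
| 20% / 10% | 0.05 mm (4%) | 0.10 mm (8%) | 0.20 mm (17%) |
| 25% / 5% | 0.10 mm (8%) | 0.20 mm (17%) | 0.40 mm (33%) |

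Percentages are of the 1.2 mm target. All three rows average 15% across arms. That allowance also has to cover women who simply quit, so giving all of it to the rule is generous to the concern.

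**3. Effect on the type I error rate**

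With 60 per arm and SD 2.40, the standard error is 2.40 × √(2/60) = 0.438 mm. Under no true effect, a bias of 0.10, 0.20 or 0.40 mm raises the two-sided error rate from 0.050 to about 0.056, 0.074 or 0.150.

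**4. Effect on power, holding the 1.2 mm difference fixed**

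Power = Φ(1.2 / (2.40 × √(2/n)) − 1.96).

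- All 71 per arm analysed: 0.846.
- After a 15% loss, 142 × 0.85 = 120.7, about 60 per arm: 0.782.

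Keeping poor compliers may dilute the difference, so the real gain in power could be smaller.

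**The case against.** The strongest reply is that dropout describes participation and intention-to-treat describes who is analysed, so the two can coexist. The only sentence in the protocol about who is analysed says intention-to-treat. The planned mixed model can also use the baseline and early-cycle scans of a woman who leaves later. This stands: a reader might infer that the rule deletes these women and flatly contradicts the analysis, but no sentence says that their scans stop or that their data are left out. The mixed model is only partial protection, however. It relies on the missing scans being explained by what was already recorded, which a compliance judgement does not guarantee, and it does nothing for the pregnancy comparison, which is by chi-squared or Fisher's exact test.

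A reader might also infer that the unblinded acupuncturist decides who is a poor complier. The protocol names no judge, and it bars the acupuncturist from exchanging grouping information with the data collection researcher. Unblinded influence is possible but not established.

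The missing compliance threshold and the missing definition of the analysis sets are details that an article may leave to the full protocol or the analysis plan. They are not part of this point.

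**Conclusion.** The point holds as an unreconciled rule, not as a proven contradiction. As written, the Dropout criteria allow a post-randomisation event that may depend on the arm to become missing primary-outcome data, and the 15% allowance suggests that dropouts are expected to be missing. Applied that way, the analysis would be closer to per-protocol than its label says.

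The size is unknown. It is zero under equal removal shares and equal gaps. It is 0.05 to 0.20 mm (4% to 17% of the target) at 20% against 10% removed with gaps of 0.5 to 2 mm, and it reaches 0.40 mm only under the more extreme 25% against 5%. If the women removed have thinner endometria and more of them come from the active arm, the bias favours electroacupuncture.

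A reader might place the whole 15% in the active arm with thickness half an SD (1.23 mm) below the arm mean, which gives 0.15 × 1.23 / 0.85 = 0.217 mm, or 18% of the target. The protocol does not support that as an estimate: it assumes that nobody is removed from sham, and it spends on poor compliance an allowance meant for all dropout in both arms.

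**What to change.** Reword the Dropout criteria so that dropout means only withdrawal of consent or loss to follow-up. State there, and again under Statistical analysis, that women who comply poorly, stop treatment or are found ineligible after randomisation keep their scheduled cycle-1 to cycle-3 scans and the 6-month contact, and are analysed in the arm to which they were randomised. Use compliance only to define a supportive per-protocol analysis. The treatment record sheet already planned under Quality control and trial monitoring could supply the attendance data.

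The cost is small: one paragraph and one sentence. Some scans will be taken in women who have stopped treatment, but those scans were already scheduled. The estimated effect may be slightly smaller, because women who received little treatment stay in the comparison.

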### Recruitment strategies

Infertile female participants with thin endometrium will be recruited either through advertisements on notice boards in Chengdu University of Traditional Chinese Medicine Affiliated Hospital or advertisements in hospital social media (WeChat). Any interested patients will reach the researcher by telephone, email, or WeChat. If they meet the study criteria, they will be invited for a face-to-face interview for baseline screening with the researcher. The researcher will explain the study in detail, including potential benefits and risks. Once a participant agrees to participate in the study, informed consent will be obtained before randomization. Participants consent forms is shown in Additional file 1.

### Randomization

The participants will be randomly assigned to electroacupuncture group or sham-electroacupuncture group in a 1:1 ratio. Randomization will be performed based on a random list of numbers generated by SPSS21.0 software (International Business Machines Corp., Armonk, NY). Allocation will be conducted by a designated researcher who has no contact with any participant and is not involved in the data collection or analysis. Allocation will be concealed in sequentially numbered, opaque, and sealed envelopes containing the randomization assignments. The appropriate numbered, opaque, sealed envelope will be opened after each participant meets eligibility criteria and signs informed consent. The allocation concealment to the doctors is not feasible for trials on acupuncture. The acupuncturist will not be allowed to reveal any information about treatment procedures and outcomes to the participants or the assessor.

